# A smartphone intervention for adolescent obesity: study protocol for a randomised controlled non-inferiority trial

**DOI:** 10.1186/1745-6215-15-43

**Published:** 2014-01-31

**Keywords:** Obesity, Smartphone, Adolescent, Behavioural intervention, Mobile health, Telemedicine

## Abstract

**Background:**

There are few evidence-based mobile health solutions for treating adolescent obesity. The primary aim of this parallel non-inferiority trial is to assess the effectiveness of an experimental smartphone application in reducing obesity at 12 months, compared to the Temple Street W82GO Healthy Lifestyles intervention.

**Methods/design:**

The primary outcome measure is change in body mass index standardised deviation score at 12 months. The secondary aim is to compare the effect of treatment on secondary outcomes, including waist circumference, insulin sensitivity, quality of life, physical activity and psychosocial health. Adolescents with a body mass index at or above the 98th percentile (12 to 17 years) will be recruited from the Obesity clinic at Temple Street Children’s University Hospital in Dublin, Ireland. W82GO is a family-based lifestyle change intervention delivered in two phases over 12 months. In the current study, participants will be randomised for phase two of treatment to either usual care or care delivered via smartphone application. One hundred and thirty-four participants will be randomised between the two study arms. An intention-to-treat analysis will be used to compare treatment differences between the groups at 12 months.

**Discussion:**

The results of this study will be disseminated via open access publication and will provide important information for clinicians, patients and policy makers regarding the use of mobile health interventions in the management of adolescent obesity.

**Trial registration:**

Clinicaltrials.gov NCT01804855.

## Background

Childhood obesity in Ireland is a major problem: 19% of 9-year-old children are overweight and 7% are obese [1]. Child and adolescent obesity is associated with multiple physical and psychological co-morbidities [2] and, although effective treatments are available, there is considerable room for improvement. For example, a Cochrane Review reported sufficient evidence for the treatment effect of well-targeted interventions and its meta-analyses found a reduction in body mass index standardised deviation score (BMI SDS) of 0.14 at 12 months [3].

The Temple Street W82GO Healthy Lifestyles programme (W82GO) is a family-based multidisciplinary outpatient treatment for child and adolescent obesity (http://w82go.ie/). In a prospective study of the W82GO programme, significant reductions in BMI SDS have been described after 12 months of treatment [4]. However, although the beneficial effects of face-to-face family-based treatment have been described [5], it remains uncertain whether such treatments can be effective when delivered to potentially greater numbers using a mobile health approach.

Data exist regarding the use of technology [6] and mobile applications in a variety of clinical areas, including patient support [7], smoking cessation [8], diabetes management [9], and cardiac rehabilitation [10], but there is a dearth of data regarding the use of mobile health approaches in the management of adolescent obesity.

## Aim

The primary aim of this project is to assess the impact of a smartphone application compared with usual care on BMI SDS over 12 months in adolescents who are obese (12 to 17 years). Secondary outcome measures are waist circumference, insulin sensitivity, quality of life, physical activity and psychosocial health.

## Methods/design

### Trial design

Randomised trial of 12 months duration with parallel groups and assessor blinding.

### Participants

Children and adolescents attending Temple Street Children’s University Hospital in Dublin Ireland for obesity management will be recruited. Children are referred to the obesity clinic by their general practitioner, or primary healthcare team.

#### ***Eligibility criteria***

• Inclusion criteria: child aged between 12 and 17 years, child BMI >98th percentile, child fluent in English, parent(s) willing to participate in the programme with their child and completion of written informed consent and assent prior to any study-specific procedures.

• Exclusion criteria: severe intellectual difficulties which would limit the child’s ability to engage in group activity, obesity secondary to genetic condition, limitations to engaging in physical activity (for example, active musculoskeletal injury) or use of medication known to effect body weight, limitations to using a smartphone device and known family issues that would affect general compliance and attendance at follow-up visits.

### Recruitment

Children will be recruited from medical clinics and given written information regarding the study. Families wishing to participate in the study will be asked to complete parental consent and age-appropriate child assent forms. The motivation and expectations of both adolescents and parents will be evaluated and the alternative treatment options will be discussed (such as 1:1 treatment in outpatient clinic). It will be made clear to parents and their adolescents that by participating in the study they will have a 50:50 chance of being treated in a standard manner or with the smartphone intervention for phase 2 of treatment.

Based on our calculations, we will need to recruit 134 adolescents for randomisation over an enrolment period of 18 months.

This study will be conducted in agreement with the ‘Declaration of Helsinki’. The study has ethical approval from The Children’s University Hospital Ethics Board (11–033). All parents and adolescents will give their written informed consent. Modifications to this study protocol will be communicated to all those involved in the study: data monitoring committee, trial steering committee, clinical team, study sponsor, and study funders.

### Randomisation

Adolescents who are eligible will be randomised to either a W82GO (usual care) group or a smartphone experimental group by the research team using a secure online randomisation system with full allocation concealment. They will be stratified by gender and parental obesity, and 134 adolescents will be randomised in total using a 1:1 randomisation ratio. After randomisation, adolescents will receive a study code, which will be used to analyse all the data related to that child.

### Intervention

#### ***Assessment***

In keeping with routine practice, adolescents and their parents are assessed by the multidisciplinary team, which allows the team to build trust with the family. Assessment by the multidisciplinary team includes the following.

##### 

**Paediatrician** During this visit, general information is collected concerning pregnancy, birth, and early childhood development. The medical history of the family and the child is discussed along with any concerns that the child or parents have. The causal effects of obesity are discussed along with the medical complications that exist.

The physical examination investigates the presence of acanthosis nigricans, possible dysmorphic features, and hirsutism. Pubertal status is recorded according to Tanner and laboratory tests are requested.

##### 

**Dietitian** In this visit, the nutritional intake of the child is detailed in tandem with the eating behaviours of the family. The child is given a food diary to be completed over two weekend days and one weekday in order to provide an indication of micro- and macro-nutrient intake. The session is also used to introduce information regarding nutrition and healthy eating behaviour.

##### 

**Physiotherapist** The adolescent undergoes a physical examination to screen for musculoskeletal problems (for example, impaired gait or balance) and to measure physical activity levels, blood pressure, sedentary behaviour, sleep, cardiorespiratory fitness and quality of life.

##### 

**Psychologist** This session provides an opportunity for the family to discuss their motivations for becoming healthier. The role of the parent is highlighted and practical strategies to promote a positive environment at home are discussed. Issues such as body image, bullying and self esteem are assessed.

### Outcomes

#### ***Primary outcome***

##### 

**Anthropometric parameters** Body weight is measured to the nearest 0.1 kg using an electronic scale (SECA, Vogel & Halke, Hamburg, Germany) and height to the nearest 0.1 cm with a stadiometer (SECA, Vogel & Halke) in light clothing and without shoes. Measures are taken in triplicate and mean values calculated. Waist circumference is measured with an anthropometric tape midway between the lower rib margin and the iliac crest at the end of gentle expiration. BMI is calculated as weight/height squared (kg/m^2^). Subjects are classified as obese if they plot above the 98th percentile for BMI on the Irish growth charts. The primary outcome, BMI SDS, is calculated using UK reference data (Cole LMS method).

#### ***Secondary outcomes***

##### 

**Blood sample analysis** Blood samples are taken by venipuncture after an overnight fast by an experienced paediatric phlebotomist. Fasting samples are taken to measure glucose, insulin, total cholesterol, high density lipoprotein, low density lipoprotein, triglycerides, thyroid function, glycated haemoglobin, and the liver enzymes aspartate transaminase and alanine transaminase.

##### 

**Insulin resistance** The Homeostasis Assessment Model for insulin resistance formula [11] is used as an index of insulin resistance:

$$\left(\mathrm{fasting}\;\mathrm{insulin}\left(\mathrm{mU}/\mathrm{ml}\right)\times \mathrm{fasting}\;\mathrm{glucose}\left(\mathrm{mmol}/l\right)\right)/22.5$$

##### 

**Blood pressure** Blood pressure measurements (Omron, Kyoto, Japan) are taken in a relaxed sitting position, in triplicate. The last measurement is used for analyses [12].

##### 

**Physical activity** Objective measurement of physical activity will be completed using 7 days of accelerometry data (Geneactiv accelerometer, Activinsights, Kimbolton, UK). The Physical Activity Questionnaire for Adolescents will be used to measure subjective physical activity in adolescents. This is a 7-day self-report measure, which is reliable and valid for use in adolescents aged 7 to 19 years [13].

##### 

**Physical fitness** Cardiorespiratory fitness is measured with a submaximal treadmill test (modified Balke test) with heart rate, rate of perceived exertion and oxygen saturation monitoring [14]. The test takes between 10 and 15 minutes or until 85% of the maximum heart rate is achieved.

##### 

**Musculoskeletal screen** The physiotherapist screens the musculoskeletal system in order to identify any issues that might cause physical limitation to the child. The screening procedure has been detailed in full previously [15]. If there are musculoskeletal concerns identified, the symptoms will be treated as appropriate. Motor skill is evaluated using the balance and coordination subscale of the Bruinnincks Oteresky Test of Motor Proficiency (Pearson, TX, USA).

##### 

**Health-related quality of life** The Pediatric Quality of Life Inventory is used as a measure of health-related quality of life and has been used in obese cohorts previously [16].

##### 

**Psychosocial health** Social, behavioural and emotional functioning is assessed using the Child behaviour Checklist/Youth Self Report [17] and self concept by The Piers Harris Questionnaire [18].

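### The insulin-resistance formula gives fasting insulin in mU/ml, but its divisor of 22.5 belongs with mU/l, so values derived literally are 1000 times too small (minor).

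*Protocol article*

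**What the plan says.** The Aim section of the protocol article lists the secondary outcomes: "Secondary outcome measures are waist circumference, insulin sensitivity, quality of life, physical activity and psychosocial health". The Abstract also names insulin sensitivity as a secondary outcome.

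The derivation is given once, under Secondary outcomes, in the paragraph on insulin resistance: "The Homeostasis Assessment Model for insulin resistance formula [11] is used as an index of insulin resistance". The displayed formula that follows has three elements:

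- fasting insulin, labelled mU/ml;
- fasting glucose, labelled mmol/l;
- a divisor of 22.5 applied to their product.

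The blood-sample paragraph in the same section says which analytes are taken ("Fasting samples are taken to measure glucose, insulin, total cholesterol", followed by others) but gives no laboratory unit for insulin. Nowhere does the article give a second insulin unit, a conversion, a worked example or an expected value of the index.

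**The concern.** The constant in this index is tied to its units. It scales the index to 1 at a reference insulin and glucose, so changing the insulin unit without changing the constant rescales every result. The constant printed here is the one for insulin in mU/l, while the unit printed beside it is a thousand times larger.

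This formula is the only operative definition in the article of an outcome named in the Aim. If an analyst converted the laboratory result to the printed unit before applying it, the reported level of insulin resistance in each arm, the difference between arms and its interval would all be on the wrong scale. They could not be set beside results for the same index from other studies.

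**Working it through.** **Inputs**

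- From the formula under Secondary outcomes: insulin unit mU/ml, glucose unit mmol/l, divisor 22.5.
- Unit conversion: 1 mU/ml = 1000 mU/l, and 1 mU/l = 1 microU/ml.
- From the standard definition of the named index, not printed in the article: 22.5 is the product of a reference insulin of 5 mU/l and a reference glucose of 4.5 mmol/l.
- Assumed for illustration, because the article gives no insulin or glucose values: insulin 5 to 40 mU/l, glucose 4.5 to 5.5 mmol/l.

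The article states no value of the index, so there is no figure of the plan's own to reproduce. The check is one of dimensional consistency.

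**Step 1: which unit fits the divisor**

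With insulin in mU/l: 5 × 4.5 / 22.5 = 1.

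With insulin in mU/ml, the same sample is 0.005 mU/ml: 0.005 × 4.5 / 22.5 = 0.001.

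To reach an index of 1 at glucose 4.5 mmol/l with the printed unit, insulin would have to be 22.5 / 4.5 = 5 mU/ml, which is 5000 mU/l. If mU/ml were kept, the matching divisor would be 22.5 / 1000 = 0.0225.

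**Step 2: size of the discrepancy**

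| Insulin (mU/l, assumed) | Glucose (mmol/l, assumed) | Index, insulin in mU/l | Index, insulin in mU/ml as printed |
|---|---|---|---|
| 5 | 4.5 | 5 × 4.5 / 22.5 = 1.0 | 0.0010 |
| 20 | 5.0 | 20 × 5.0 / 22.5 = 4.44 | 0.020 × 5.0 / 22.5 = 0.0044 |
| 40 | 5.5 | 40 × 5.5 / 22.5 = 9.8 | 0.0098 |

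The ratio is 1000 in every row. It comes from the unit conversion alone, so it does not depend on the assumed values.

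**Step 3: what a constant factor does to the analysis**

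Write H for the index with the matching unit, so that the index as printed is H/1000.

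- Arm means, the mean difference d, its standard error SE and the confidence limits are all divided by 1000.
- The test statistic is (d/1000) / (SE/1000) = d/SE, which is unchanged, and so is the p-value.
- A ratio of arm means is unchanged, because the factor appears in numerator and denominator.
- A standardised difference is unchanged, because the standard deviation is also divided by 1000.
- On a log scale, log(H/1000) = log H − log 1000. This is the same shift for every participant, so differences between arms are unchanged.

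**The case against.** Three points on the other side deserve weight.

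First, the article does not contradict itself on this: it prints one unit once, and the pairing of 22.5 with mU/l appears nowhere in it. That is true, but the constant is part of what the named index is, much as kg/m² is part of what BMI is. The cited source is not needed to see that the unit and the constant do not fit.

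Second, mU and microU differ by one character. A micro sign may have turned into an m in typesetting or when the text was converted. The text available cannot exclude this. The formula as read is nevertheless unambiguous, and if the printed article carries the same unit it still needs correcting.

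Third, the factor of 1000 arises only if someone converts the laboratory result to mU/ml. The article describes no such step. If the laboratory reports mU/l or microU/ml and that number is entered directly, the index is right and only the label is wrong. This stands, and it is the main reason for treating the point as minor.

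A reader might infer more: that the slip would spoil the handling of skewed data, leave values lost to rounding, or misclassify participants against a threshold. The article does not support any of these. The Data analysis section provides for transformation or non-parametric methods such as the bootstrap without naming a particular transformation. No section sets a reporting precision or defines a threshold for this index.

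**Conclusion.** The formula is wrong as written, and the point is minor. Taken literally, it puts every value of this secondary outcome, together with the arm means, the mean difference and the confidence interval, 1000 times too low: for example 0.0044 instead of 4.44 at an assumed insulin of 20 mU/l and glucose of 5.0 mmol/l. P-values, ratios, standardised differences and the direction of any effect stay the same.

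The conclusion rests on the standard definition of the named index. The factor of 1000 does not rest on the illustrative insulin and glucose values. Whether any computed result is affected depends on the unit in which the laboratory figure enters the derivation, which the article does not say.

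It would be wrong to read this as a threat to the trial's main conclusion. The primary outcome is BMI SDS, and the Power calculation section uses only BMI SDS figures. It would equally be wrong to conclude that the insulin-resistance data will be miscalculated; a slip in the printed unit is the likelier explanation.

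**What to change.** In the formula under Secondary outcomes, change the insulin unit to mU/l (equivalently microU/ml), leaving glucose in mmol/l and the divisor at 22.5. Before deriving the index, confirm that the unit in which the laboratory reports insulin matches, and check the derivation against one hand-calculated case, such as 20 × 5.0 / 22.5 = 4.44.

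The cost is a one-line correction to the outcome definition and a short check of the derivation. It needs no participants, samples or visits beyond those planned.

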### Treatments

W82GO is underpinned by behavioural change theory (transtheoretical model and social cognitive theory) and uses strategies including stimulus control, self-monitoring, positive reinforcement, goal setting and problem solving to facilitate lifestyle change. The intervention is described in full in Additional file 1. W82GO consists of phase 1 and phase 2 treatments.

#### ***Phase 1 treatment***

Phase 1 is the initial intensive phase and consists of six weekly sessions (0 to 6 weeks) for adolescents and their parents. These sessions last 2 hours and incorporate educational and practical sessions to increase physical activity, improve nutrition, increase sleep and reduce obesity.

#### ***Phase 2 treatment***

Phase 2 is a maintenance phase. Upon completion of phase 1, participants return with their parents for three 3-monthly booster maintenance sessions over 46 weeks [4]. These sessions are aimed to encourage the family to continue with lifestyle change and to manage barriers to change.

In the current study, having completed phase 1 of treatment, participants will be randomised for phase 2 to either usual care or smartphone care.

The smartphone application incorporates evidence-based behavioural change tools such as self-monitoring, goal setting, and peer support. Evidence-based tips are sent to the user in the form of a text tip, a video tip or an image tip. The tips aim to increase the knowledge of the participant with regard to healthy eating, physical activity, physical fitness and sleep. The user is encouraged to engage in daily goal setting to increase physical activity level and sleep, increase water intake, reduce intake of sugar and fat and to increase intake of fibre, fruits and vegetables. In addition, the user is encouraged to monitor their progress by reviewing their goals daily and by entering their height and weight measurements (which are charted over time).

Those randomised to usual care will return for three booster sessions and for measurement of primary and secondary outcomes at 6 and 12 months. Those in the smartphone group will use the smarphone app and will return for measurement of outcomes at 6 to 12 months. Contact with the participants will be ensured throughout the study by monthly phone-calls from the principal investigator. See Figure 1.

**Figure 1 F1:**
[figure not shown]
Study flow chart.

### Power calculation

This study is a non-inferiority trial to determine whether a smartphone intervention could be used as a treatment in adolescent obesity management. The null hypothesis is that the smartphone intervention will have a positive effect on BMI SDS but that this change will be inferior to usual care. Based on a 0.21 reduction of BMI SDS at 12 months, a standard deviation of 0.24 in the usual care group and a non-inferiority limit of 0.12, the sample size required at 80% power will be 50 per group or 100 total. To allow for expected dropout the total number of adolescents to be recruited will be 134.

### Blinding

After randomisation and assignment to the study group, participants will be given a study identification number. The assessor of the primary outcome will not know the allocated intervention for the participant, to reduce the risk of bias. Given the nature of the intervention, it is not possible to blind the participants or the care providers. An independent data analyst will be blinded during the trial by the use of a fully anonymised dataset.

### Electronic health considerations

Given the dynamic nature of electronic health trials, there may be changes to the methodology after trial commencement and, if so, these will be detailed in full. Examples include major bug fixes in the software, changes in the functionality or content of the application and any unexpected events that might influence study outcomes (such as system failures or downtimes).

### Data collection and management

Primary and secondary outcome measurement will take place during initial baseline assessment, at 6 months and at 12 months. Participants who drop out of the trial will be invited to attend these follow-up visits for measurement. Data will be stored on password-protected firewalled computers, which are accessible only to members of our research team and those involved in managing the application software. Blood samples will be labelled with the patient’s initials and medical record number and stored in laboratories that are locked when not in use. With the permission of the participant (or parent/guardian), the blood samples and information collected during this research study may be stored indefinitely and used by our research group for future studies. Any information about individual participants derived from the additional studies will be kept confidential. The participant may at any time request that the blood samples be destroyed. When the results of the research are published or discussed in conferences, no information will be included that would reveal the identity of any participant unless their specific consent had been obtained. Data will be entered using double-data entry to assure quality control.

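### No BMI SDS measurement is scheduled at randomisation, so the 12-month change carries phase 1 response common to both arms, which costs precision but causes no bias

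*Protocol article*

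**What the plan says.** Data collection and management lists the outcome time points: "Primary and secondary outcome measurement will take place during initial baseline assessment, at 6 months and at 12 months". The section on phase 1 places the intensive treatment first: "Phase 1 is the initial intensive phase and consists of six weekly sessions (0 to 6 weeks) for adolescents and their parents". The section on phase 2 puts allocation after it: "having completed phase 1 of treatment, participants will be randomised for phase 2 to either usual care or smartphone care". It then describes usual care in phase 2, in which "participants return with their parents for three 3-monthly booster maintenance sessions over 46 weeks". The abstract gives the overall span: "W82GO is a family-based lifestyle change intervention delivered in two phases over 12 months".

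The primary outcome is the change in BMI SDS at 12 months (abstract). The Data analysis section adjusts for age, BMI and gender at baseline. The Power calculation section uses a 12-month reduction of 0.21, an SD of 0.24 and a margin of 0.12.

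One wording difference sits in the phase 2 section. Usual care is measured at 6 and at 12 months, while the smartphone group "will return for measurement of outcomes at 6 to 12 months".

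**The concern.** The arms differ only in phase 2, but the declared change is counted from before phase 1. Each child's 12-month change is then the sum of a phase 1 part, which precedes allocation and cannot be a treatment effect, and a phase 2 part, which is what the trial randomises. The phase 1 part adds spread to the primary contrast. By chance its mean may also differ between the arms, and that difference passes into the estimate. Adjusting for initial BMI does not deal with this, because that value was taken before the response occurred.

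Two things are at stake: precision in a trial planned at only 80% power, and the ability to report how each arm changed from the moment of allocation. An analysis plan cannot supply this later, since it cannot analyse a measurement that was never taken.

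**Working it through.** **Timing.** Phase 1 covers weeks 0 to 6 and phase 2 lasts 46 weeks. 6 + 46 = 52 weeks, which matches a 12-month programme. So the 12-month clock starts with phase 1, and randomisation falls at about week 6. That the baseline precedes phase 1 is an inference from this sum, from the week numbering and from the description of the baseline assessment as initial. No sentence says so outright.

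**The plan's own figure.** Inputs from the Power calculation section: margin 0.12, SD 0.24, power 80%; a true difference of 0 is assumed. The document states no alpha.

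n per group = 2 × (z_alpha + z_power)² × SD² / margin²

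- One-sided 5%: 2 × (1.645 + 0.842)² × 0.0576 / 0.0144 = 49.5, so 50 per group. This reproduces the plan.
- One-sided 2.5%: 2 × (1.960 + 0.842)² × 4 = 62.8, so 63 per group. This does not.

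The rest uses one-sided 5%.

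**Effect of a covariate at randomisation.** Let s1 and s2 be the SDs of phase 1 and later change, and r their correlation. Hold the total at the plan's value: s1² + s2² + 2·r·s1·s2 = 0.24² = 0.0576. Then:

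- s2 = −r·s1 + √(0.0576 − s1²·(1 − r²))
- variance removed by conditioning on phase 1 change = (s1 + r·s2)²
- power = Φ(0.12 / (residual SD × √(2/50)) − 1.645), where √(2/50) = 0.2

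With nothing removed: 0.12 / (0.24 × 0.2) = 2.5, and Φ(2.5 − 1.645) = 80%.

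Neither s1 nor r is in the document. The values below are assumptions.

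| r | s1 | s2 | Variance removed | Residual SD | Power |
|---|---|---|---|---|---|
| 0 | 0.08 | 0.226 | 0.0064 (11%) | 0.226 | 84% |
| 0 | 0.12 | 0.208 | 0.0144 (25%) | 0.208 | 89% |
| −0.3 | 0.08 | 0.252 | 0.00002 (0%) | 0.240 | 80% |
| −0.3 | 0.12 | 0.247 | 0.0021 (4%) | 0.236 | 82% |
| +0.2 | 0.08 | 0.211 | 0.0149 (26%) | 0.207 | 90% |
| +0.2 | 0.12 | 0.185 | 0.0247 (43%) | 0.181 | 95% |

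**Covariate or new change score.** At r = −0.3, s2 (0.252 or 0.247) exceeds 0.24. Replacing the outcome by raw change from randomisation would then lower power to Φ(0.12/0.0503 − 1.645) = 77% or Φ(0.12/0.0494 − 1.645) = 78%. Covariate adjustment does not fall below the current 80% in any row of the table.

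**Chance imbalance.** The standard error of the between-arm difference in mean phase 1 change is s1 × 0.2 = 0.016 to 0.024. That is 13% to 20% of the 0.12 margin.

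**The case against.** The strongest reply is that nothing in the primary comparison is wrong. Phase 1 is common to both arms and precedes allocation, so the expected between-arm difference in 12-month change equals the expected difference in phase 2 change. A covariate six weeks old is still a valid covariate. The planning SD is given beside a 12-month reduction and so appears to cover the whole programme; if so, the stated 50 per group already pays for the phase 1 spread. All of this stands. A reader might infer bias or a wrong sample size from the timing, and the document supports neither.

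A reader might also infer that no BMI SDS value exists at randomisation, or that balance between the arms cannot be checked. Both go too far. The document schedules no such value, but Figure 1 and Additional file 1, which holds the full description of the intervention, are not shown. Initial characteristics precede allocation and can be compared between arms, and allocation is stratified by gender and parental obesity. Only balance on BMI SDS after phase 1 is out of reach. Likewise, the between-arm phase 2 effect is estimated, and the change from 6 to 12 months lies wholly within phase 2. What cannot be reported is within-arm change from randomisation.

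Finally, the power gain rests on an assumed phase 1 SD and an assumed correlation. With rebound after phase 1 the gain nearly disappears. That also stands, and it is why the gain is given as a range.

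**Conclusion.** The point holds as a cheap improvement in precision and reporting, not as an error in the comparison. On the document's own timing, the 12-month change includes about six weeks of response from before randomisation, and the planned adjustment cannot remove it. Under the assumptions shown (total SD 0.24, 50 per group, one-sided 5%, phase 1 SD 0.08 to 0.12), a covariate at randomisation moves power from 80% to 84-89% under independence, to about 80-82% at a correlation of −0.3, and to 90-95% at +0.2. Apart from a negligible loss of degrees of freedom, it does not reduce precision.

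A reader might go further and conclude that the margin covers the whole phase 2 effect of usual care. That would need phase 1 to supply at least (0.21 − 0.12) / 0.21 = 43% of the 0.21 reduction. The document does not split that figure, so the conclusion is not supported.

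The difference between the two follow-up descriptions in the phase 2 section is editorial only. Data collection and management gives the same time points without distinguishing the arms. It adds no weight to this point.

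**What to change.** Measure height and weight at the last phase 1 session, before allocation. Add the resulting BMI SDS to the primary model as a covariate beside the initial baseline BMI SDS. Keep the total 12-month change as the declared outcome, and report within-arm change from randomisation descriptively.

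The trial is recruiting, so some children may already have been randomised without this value. For them, keep the initial value in its own covariate and treat the value at randomisation as missing, using a missing indicator or imputation. Do not put the initial value in its place: that would mix measurements from before and after phase 1 in one covariate. Because the missing item precedes randomisation, its absence cannot be a consequence of allocation.

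The cost is a few minutes of measurement at a session that families already attend, a minor amendment and a sentence in the analysis plan.

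Separately, reconcile the two descriptions of follow-up timing in the phase 2 section so that both arms have the same stated time points.
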